#### Collection and determination of 24 hour urine specimens

2.5.4

Keep a normal diet and avoid strenuous exercise before urine retention. Record the start and end time of urine retention and use a wide-caliber container to collect urine for 24 hours. After mixing, measure and record the total urine volume. The urine sodium, urine potassium, and urine protein were measured in the laboratory of Chengdu Fifth People's Hospital and the 24-hour urine sodium excretion and 24-hour urine MA volume were calculated.

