**Objective::**

The purpose of this study is to compare 24-hour urine sodium excretion, BPV, carotid intima–media thickness, left ventricular mass index, and serum creatinine or endogenous creatinine clearance rate. To clarify the relationship between high salt load and BPV and TOD in patients with hypertension.

This study is a cross-sectional study. It will recruit 600 patients with essential hypertension in the outpatient and inpatient department of cardiovascular medicine of Chengdu Fifth People's Hospital. Researchers will obtain blood and urine samples with the patient's informed consent. In addition, we will measure patient's blood pressure and target organ-related information.

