#### Target organ measurement standard

2.5.5

1.Blood vessels: Detection of carotid IMT: The patient lies on his back and turn the head to the opposite side. The distance between the intimal surface of the common carotid artery bifurcation 1 cm non-plaque and the outside of the median was measured, and the maximum value was taken on both sides. According to the relevant diagnostic criteria in the 2010 Chinese guidelines for the management of hypertension, the carotid intima media thickness >0.9 mm is defined as thickening and the local protrusions protrude from the arterial lumen >0.5 mm or IMT > 1.5 mm is defined as carotid atheromatous plaque.2.Heart: LVMI: Measure the left ventricular end diastolic diameter (LVDd), interventricular septum, and left ventricular posterior wall, measure 3 consecutive cardiac cycles and take the average. According to the Devereux formula, calculate left ventricular mass (LVM) and LVMI: LVM (g) = 0.8 × 10.4 × ([IVST + PWT + LVDd]^3^ − LVDd^3^) + 0.6; LVMI = LVM / body surface area.3.Kidney: Serum creatinine or endogenous Ccr: 24-hour urine A. MA is defined as negative urine routinely detected protein, and urinary albumin excretion rate is 30 to 300 mg/24 hour.

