#### Grouping criteria

2.5.6

Twenty-four-hour urinary sodium was used to estimate sodium salt intake. Based on the quartiles of the 24-hour urine sodium, the enrolled population was divided into low sodium group, low-to-medium sodium group, medium-to-high sodium group, and high sodium group.

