### Statistical methods

2.7

We will use SPSS 17.0 software for statistical analysis in this study. Normal distribution measurement data was expressed as mean ± SD. One-way analysis of variance was used for comparison of means among multiple groups, and SNK test was used for pairwise comparison. The measurement data of non-normal distribution is expressed as median M (P25–P75). After the natural logarithm is converted to the normal distribution data for analysis, the nonparametric statistical method is used for comparison between groups. Nonparametric test was used to compare data between groups. Correlation analysis used Pearson correlation analysis. Covariance analysis was used to compare the differences in BPV between groups, and multiple stepwise regression analysis was performed on target organ factors related to BPV. *P* < .05 is statistically significant.

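### Sodium exposure and 24-h microalbumin (and presumably Ccr) come from one urine collection with no stated acceptance rule and no urine creatinine, so shared collection error can mimic a salt-kidney association

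*Protocol article*

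**What the plan says.** **Collection (Protocol article, 2.5.4).** One timed collection is described: "Record the start and end time of urine retention and use a wide-caliber container to collect urine for 24 hours". Volume is handled as follows: "After mixing, measure and record the total urine volume". The assay list is: "The urine sodium, urine potassium, and urine protein were measured in the laboratory". The same sentence says that 24-h sodium excretion and 24-h MA are calculated. Urine creatinine is not listed, Ccr is not mentioned, and no limit is attached to duration or volume.

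**Exposure (2.5.6).** "Twenty-four-hour urinary sodium was used to estimate sodium salt intake". The groups follow from it: "Based on the quartiles of the 24-hour urine sodium, the enrolled population was divided into low sodium group", and so on up to the high sodium group.

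**Kidney outcomes (2.5.5, item 3).** "Serum creatinine or endogenous Ccr: 24-hour urine A", where the last letter is evidently a truncated MA. MA is defined on an absolute scale, 30 to 300 mg per 24 hours. The Objective and the Introduction also offer serum creatinine and Ccr as alternatives.

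**Analysis (2.7).** Pearson correlation and comparisons across groups, with P "< .05 is statistically significant".

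**Contrast (2.5.3).** Ambulatory blood pressure recordings do have stated validity limits: more than 85% of scheduled readings, more than 48 valid values, and plausible ranges.

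**The concern.** A 24-h excretion is a concentration multiplied by the collected volume. If a patient returns only a fraction f of the day's urine, measured sodium and measured MA are both multiplied by f. So is Ccr, if it is computed from that urine. Missed voids, or a collection that runs short or long, then move exposure and outcome in the same direction. Error of this kind does not average out. It produces positive correlation between quantities that may be unrelated.

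The two kidney results would also point in opposite clinical directions. Higher sodium would appear to go with better filtration (higher Ccr) and with more albuminuria. Neither Pearson correlation nor a comparison across sodium quartiles can separate this from a real relation, and the salt-organ damage relation is the stated aim (2.1).

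There is also an internal mismatch. Endogenous Ccr is a named marker, but it needs urine creatinine, which the assay list does not include.

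**Working it through.** The article gives no power calculation, spread or completeness rate, so there is no stated figure to reproduce. The check asks how often a null salt-kidney relation would be declared significant.

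**Inputs from the article.** N = 600 (Objective: "It will recruit 600 patients with essential hypertension in the outpatient and inpatient department of cardiovascular medicine"), hence 600/4 = 150 per sodium quartile. Alpha is 0.05, taken as two-sided because sidedness is not stated.

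**Assumptions, not in the article.** The spreads of sodium, Ccr and albumin, the frequency of incomplete collections, and the degree of loss.

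**Check 1: closed form.** On the log scale, let s be the SD of collection error, 0.40 the SD of true sodium, and so the SD of the true outcome (0.25 for Ccr, 1.0 for albumin). With no true association:

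r = s² / √[(0.40² + s²)(so² + s²)]

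P(P < .05) = Φ(z − 1.96) + Φ(−z − 1.96), where z = atanh(r) × √(600 − 3).

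Example, Ccr with s = 0.10: r = 0.01/√(0.17 × 0.0725) = 0.090; z = 0.0903 × 24.43 = 2.21; probability ≈ 60%.

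Example, MA with s = 0.20: r = 0.04/√(0.20 × 1.04) = 0.088; z = 2.15; probability ≈ 57%.

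| s | r, sodium-Ccr | P < .05 | r, sodium-MA | P < .05 |
|---|---|---|---|---|
| 0.10 | 0.09 | 60% | 0.02 | 9% |
| 0.15 | 0.18 | 99% | 0.05 | 25% |
| 0.20 | 0.28 | 100% | 0.09 | 57% |

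**Check 2: simulation with incomplete collections.** There were 2000 replicates of 600 patients. True sodium (CV 0.40), Ccr (CV 0.25) and albumin excretion (median 15 mg/24 h, log-SD 1.0) were independent log-normals. A share of patients had all three multiplied by the same f, uniform on 0.5-0.9 (marked loss) or 0.7-0.95 (mild loss). The tests were Pearson, with albumin logged. At N = 600 significance needs |r| > 0.080.

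| Loss | Incomplete | mean r, Na-Ccr | false positive | mean r, Na-ln(MA) | false positive |
|---|---|---|---|---|---|
| None | 0% | 0.00 | 4.5% | 0.00 | 4.1% |
| Mild | 10 / 20 / 30% | 0.04 / 0.06 / 0.08 | 14 / 31 / 50% | 0.01 / 0.02 / 0.02 | 7 / 8 / 9% |
| Marked | 10 / 20 / 30% | 0.09 / 0.16 / 0.21 | 58 / 98 / 99.9% | 0.03 / 0.06 / 0.07 | 10 / 27 / 42% |

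One-way ANOVA across sodium quartiles gives similar results: for Na-Ccr under marked loss, 52 / 97 / 99.9%. With wider spreads (CVs 0.5 and 0.3, albumin log-SD 1.2; 20% incomplete, marked loss) the Pearson rates are 76% for Ccr and 16% for MA.

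On the MA threshold, with 20% incomplete and marked loss, 19.8% of the lowest sodium quartile reach 30 mg/24 h against 24.0% of the highest. With complete collections both are 24.4%.

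**Check 3: does the remedy work?** Dividing albumin by creatinine from the same urine cancels f. With incomplete collections left in, the false-positive rate for sodium against the logged ratio stays at 4-5%. This treats creatinine excretion as unrelated to sodium intake.

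**Check 4: dilution elsewhere.** BPV, IMT and LVMI do not depend on the urine, so error in sodium only shrinks their correlations, by √[0.16/(0.16 + s²)]. For s = 0.10 / 0.15 / 0.20 this is 0.97 / 0.94 / 0.89, a loss of 3 / 6 / 11%.

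**The case against.** The strongest reply is that a condensed article may leave collection rules to other documents. Section 2.6 refers to a written protocol, standard operating procedures, data validation and regular checks, none of them shown. That stands as far as it goes: a completeness rule may exist, and its absence from the article would not be a finding by itself. Two things are not omissions, however. Taking exposure and outcome from one container in absolute daily amounts is a stated design choice, and a completeness screen would reduce the shared error without removing it. The explicit assay list also does not support a marker that the article names.

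Several stronger readings are tempting but not supported:

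- *Ccr is stated to come from this urine.* It is not. Section 2.5.4 names only sodium excretion and MA as calculated. The link is an inference, because a clearance needs timed urine and no other collection is described.
- *The filtration marker is necessarily affected.* Serum creatinine is a stated alternative and does not depend on collected volume. The article leaves the choice open.
- *Every collection enters the quartiles unscreened, and no check is possible.* The article says neither. Recorded times and volume allow checks on both; only a creatinine-based check is ruled out by the listed assays.
- *A spurious result is certain.* The size depends on collection quality, which is not given. For MA, the one outcome explicitly tied to this urine, the rate is close to nominal under mild loss.
- *The other organ comparisons are badly compromised.* A loss of 3-11% in correlation is modest.

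**Conclusion.** The point holds in a limited form. As written, the plan permits a positive sodium-MA association, and a positive sodium-Ccr association if Ccr comes from this urine, to arise from collection error alone. The listed assays can yield neither Ccr nor a creatinine-based completeness check.

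The Ccr problem is potentially large: above nominal in every scenario with incomplete collections, and near certain under marked loss in 20% or more of them. The MA problem is small under mild loss and material only under marked loss. All these rates rest on assumed spreads and loss patterns and on a true null, so they show what could happen, not what will. The direction of the bias depends only on the shared volume. The plan should be changed on this point, but the study's other comparisons are not in serious doubt because of it.

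**What to change.** 1. Add urine creatinine to the section 2.5.4 assays, on the same specimen, and say which urine Ccr is computed from.
2. Before forming quartiles, apply a prespecified completeness rule based on recorded duration, volume and creatinine excretion, and state how failing collections are handled. Correct the rest to 24 hours from the recorded times. This deals with mistimed collections but not with missed voids, which is why items 3 and 4 are also needed.
3. In the salt-kidney analyses use serum creatinine or eGFR, not Ccr, as the filtration marker. Section 2.3.1.2 already requires eGFR for eligibility.
4. Keep 24-h MA as defined in section 2.5.5 and report the albumin/creatinine ratio alongside it as a sensitivity analysis. Wholesale replacement is not needed.

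**Cost.** One routine assay and the loss of some collections. The ratio depends on muscle mass through creatinine output, so it is a cross-check and not a bias-free substitute. The assay is cheap only while urine is available. Sections 2.2 and 2.4 give different periods (April 2020 to March 2022, and July 2017 to July 2018), so the sponsor should confirm whether any specimens have already been processed.

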#### Target organ measurement standard

2.5.5

1.Blood vessels: Detection of carotid IMT: The patient lies on his back and turn the head to the opposite side. The distance between the intimal surface of the common carotid artery bifurcation 1 cm non-plaque and the outside of the median was measured, and the maximum value was taken on both sides. According to the relevant diagnostic criteria in the 2010 Chinese guidelines for the management of hypertension, the carotid intima media thickness >0.9 mm is defined as thickening and the local protrusions protrude from the arterial lumen >0.5 mm or IMT > 1.5 mm is defined as carotid atheromatous plaque.2.Heart: LVMI: Measure the left ventricular end diastolic diameter (LVDd), interventricular septum, and left ventricular posterior wall, measure 3 consecutive cardiac cycles and take the average. According to the Devereux formula, calculate left ventricular mass (LVM) and LVMI: LVM (g) = 0.8 × 10.4 × ([IVST + PWT + LVDd]^3^ − LVDd^3^) + 0.6; LVMI = LVM / body surface area.3.Kidney: Serum creatinine or endogenous Ccr: 24-hour urine A. MA is defined as negative urine routinely detected protein, and urinary albumin excretion rate is 30 to 300 mg/24 hour.

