## Introduction

1

Essential hypertension is a common circulatory system disease, which is affected by both genetic and environmental factors,^[1]^ and accounts for more than 40% of the cardiovascular disease total burden.^[2]^ High salt intake can not only increase blood pressure, but also reduce the efficacy of antihypertensive drugs. And 24-hour urine sodium test is the best way to measure an individual's daily sodium intake.^[3]^ Blood pressure variability (BPV) is a basic characteristic of blood pressure and can reflect the magnitude of blood pressure fluctuations over a period of time. Recent research shows that BPV can better reflect cardiovascular activity than blood pressure levels and is more closely related to target organ damage (TOD) in hypertension.^[4–6]^ Failure to detect and treat essential hypertension early can damage important organs such as the heart, brain, and kidneys, causing diseases such as left ventricular hypertrophy, atherosclerosis, and renal failure.^[7,8]^ Left ventricular hypertrophy (LVH) is an independent cardiovascular risk factor in patients with essential hypertension.^[9,10]^ Intima–media thickness (IMT) is a marker that can be used to assess the severity of atherosclerosis.^[11]^ Serum creatinine, endogenous creatinine clearance rate (Ccr) and 24-hour urine microalbumin (MA) were commonly used indicators of renal function. However, the relationship among high salt load, BPV, and TOD in patients with hypertension is unclear. This study recruited patients with essential hypertension in the Department of Cardiovascular Medicine of Chengdu Fifth People's Hospital. Collect basic patient information, blood pressure measurements, blood specimens, 24-hour urine specimens, and other clinical examination results. Carotid IMT, left ventricular mass index (LVMI), serum creatinine or Ccr, 24-hour urine MA, and other indicators were used to evaluate TOD. To clarify the relationship among high salt intake, BPV, and TOD. To lay a good foundation for early detection of TOD in essential hypertension and related measures.

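### The left ventricular mass formula is printed with 10.4 where 1.04 is needed; applied as printed, LVM and LVMI would be about ten times too high.

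*Protocol article*

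**What the plan says.** Section 2.5.5 (Target organ measurement standard), under Heart, lists the echocardiographic inputs: "Measure the left ventricular end diastolic diameter (LVDd), interventricular septum, and left ventricular posterior wall". Each is averaged over three cardiac cycles. The next instruction is: "According to the Devereux formula, calculate left ventricular mass (LVM) and LVMI". The formula follows: "LVM (g) = 0.8 × 10.4 × ([IVST + PWT + LVDd]^3", from which the cube of LVDd is subtracted inside the bracket, with 0.6 added at the end. The index is then "LVMI = LVM / body surface area".

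The result is declared to be in grams. No unit is given for the three dimensions, and no LVMI limit for hypertrophy is stated. Nothing elsewhere in the article corrects the coefficient.

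The Introduction gives LVMI its role: "Carotid IMT, left ventricular mass index (LVMI), serum creatinine or Ccr, 24-hour urine MA, and other indicators were used to evaluate TOD". LVMI is the only entry under Heart in section 2.5.5 and the only cardiac measure named in the Objective.

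**The concern.** The bracket is a difference of two cubed lengths, that is, a volume. Turning a volume into grams needs a density, and with lengths in cm the printed 10.4 stands where that density belongs. Heart muscle is close to water in density (taken here as about 1.04 to 1.06 g/cm3). The printed digits match 1.04 with the decimal point one place off.

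At stake are the values of the study's only named cardiac outcome. Section 2.7 plans means with SDs, comparisons between groups, correlation and stepwise regression. Section 2.6 says assessments are to follow the protocol and that staff receive it in writing, so a wrong constant printed there could pass straight into a worksheet or a compute statement.

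**Working it through.** **Inputs**
- From section 2.5.5: the factors 0.8 and 10.4, the additive 0.6, output in grams, and LVMI as mass over body surface area (BSA).
- Assumed, because the article gives none: septum and posterior wall 0.7 to 1.3 cm, LVDd 4.2 to 5.5 cm, BSA 1.75 m2.
- The article states no LVM or LVMI value, so there is no figure of its own to reproduce. The check is whether the printed formula can give a possible mass.

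**Formulas**
- V = (IVST + PWT + LVDd)^3 − LVDd^3
- Printed: LVM = 0.8 × 10.4 × V + 0.6 = 8.32 V + 0.6
- With 1.04: LVM = 0.8 × 1.04 × V + 0.6 = 0.832 V + 0.6

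**Worked case** (walls 1.0 and 1.0 cm, LVDd 4.8 cm)
- V = 6.8^3 − 4.8^3 = 314.432 − 110.592 = 203.84 cm3
- Printed: 8.32 × 203.84 + 0.6 = 1,696.5 g; divided by 1.75 = 969 g/m2
- With 1.04: 0.832 × 203.84 + 0.6 = 170.2 g; divided by 1.75 = 97 g/m2

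**Across hearts**

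| Walls / LVDd (cm) | V (cm3) | LVM printed (g) | LVM with 1.04 (g) | Ratio | LVMI printed / with 1.04 (g/m2) |
|---|---|---|---|---|---|
| 0.7 / 4.2 | 101.5 | 845 | 85 | 9.94 | 483 / 49 |
| 0.9 / 4.7 | 170.8 | 1,422 | 143 | 9.96 | 812 / 82 |
| 1.0 / 4.8 | 203.8 | 1,697 | 170 | 9.97 | 969 / 97 |
| 1.2 / 5.0 | 280.2 | 2,332 | 234 | 9.98 | 1,333 / 134 |
| 1.3 / 5.5 | 365.1 | 3,038 | 304 | 9.98 | 1,736 / 174 |

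**Could another length unit make 10.4 right?** For the worked heart, the printed formula gives about 1,696,000 g in mm, 1,697 g in cm, 104 g in inches and 2.3 g in dm, against 170 g. The dm result is about 74 times too small (170.2 / 2.3). Ignoring the 0.6 g, 10.4 would be right only for a length unit of 10^(1/3) = 2.154 cm, which is no unit in use.

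**Effect on the planned analyses.** The two versions are tied by an exact identity: printed LVM = 10 × (LVM with 1.04) − 5.4, since 10 × (0.832 V + 0.6) − 5.4 = 8.32 V + 0.6. Dividing by BSA leaves a small offset of 5.4 / BSA, about 3 g/m2 at 1.75 m2. The error is therefore almost a pure change of scale.
- Means, SDs and untransformed group differences become about ten times too large.
- Unstandardised regression coefficients become about ten times too large if untransformed LVMI is the outcome, and about ten times too small if it is a predictor.
- On the natural-log scale the factor becomes a nearly constant shift of about 2.30 (ln 9.97), so differences and slopes hardly move.
- Correlations, standardised coefficients and P values hardly move. In a simulated sample of 600 (walls about 1.0 cm, mean LVDd 4.8 cm, mean BSA 1.7 m2), the correlation of LVMI with a covariate was 0.1585 with 10.4 and 0.1584 with 1.04.

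**The case against.** The strongest reply is that this may be no more than a typing slip in the article. The text names the formula it means to use, and the written procedures mentioned in section 2.6 are not shown; the echo software or analysis code may already use 1.04. That stands. The article cannot settle which constant is computed, so the consequence holds only if the formula is applied as printed. It does not make the printed formula right.

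A second reply is that the study asks about relationships, and those survive a change of scale. This also stands for correlations, tests and P values, but not for reported values in g/m2. It also means that no planned test would show that something had gone wrong.

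A reader might also draw stronger conclusions, which the article does not support:
- *All patients will be classed as having hypertrophy, so the cardiac outcome loses its variation.* Section 2.5.5 gives cutoffs for carotid thickness and albumin excretion but none for LVMI, and section 2.7 plans no analysis of hypertrophy as a yes/no outcome. The Introduction mentions hypertrophy only as background.
- *Every regression coefficient is inflated tenfold.* Section 2.7 does not make clear whether LVMI is outcome or predictor, and it provides for log transformation of non-normal data. The coefficient could be too large, too small or almost unchanged.
- *The added 0.6 g proves that 1.04 was meant.* It is negligible beside either 170 g or 1,697 g and discriminates nothing. The evidence is the density and the impossible masses.

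**Conclusion.** Wrong as written. The coefficient in section 2.5.5 has a misplaced decimal point, and none of the length units tried rescues it. Applied as printed, LVM and LVMI would be 9.94 to 9.98 times the value obtained with 1.04. That ratio hardly depends on the assumed heart dimensions and not at all on BSA. The absolute figures (1,697 against 170 g; 969 against 97 g/m2) do depend on assumed inputs.

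The damage would fall on LVMI means, SDs, untransformed group differences and unstandardised coefficients involving untransformed LVMI. Any later comparison with an absolute hypertrophy limit would also be invalid, although the article states no such limit. The significance tests and correlations would stand almost unchanged. LVMI is the only cardiac measure named; the Introduction leaves room for unspecified further indicators.

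**What to change.** In section 2.5.5, change 10.4 to 1.04 and state that septum, posterior wall and LVDd are all entered in cm. Check which constant and which length unit the echo worksheet and the SPSS compute step use. If any LVMI has already been derived with 10.4, recalculate it from the stored dimensions and BSA. If the derivation already uses 1.04, only the text needs correcting.

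The cost is one number and one unit statement in the protocol, plus a check of the derivation syntax. No new data are needed.

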##### Exclusion criteria

2.3.1.2

Participants who will meet any of the following will be excluded:

(1)Acute or chronic renal insufficiency: eGFR ≤45 mL/minute(2)Severe cardiovascular disease(3)Exclude patients with malignant tumors, hematological diseases, rheumatic immune system diseases(4)Heart failure (systolic)(5)Take routine dose or overdose of diuretics continuously for 2 weeks (but the fixed compound of RASI + 12.5 mg thiazide diuretics can be included).

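### The filtration endpoint is serum creatinine or Ccr, with no rule for choosing and no body-size handling, so the two can disagree across sodium quartiles when salt has no effect

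*Protocol article*

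**What the plan says.** The protocol article states the filtration measure as an alternative in three places. Section 2.5.5, item 3, has "Kidney: Serum creatinine or endogenous Ccr". The Objective in the Abstract has "serum creatinine or endogenous creatinine clearance rate". The Introduction says that "serum creatinine or Ccr, 24-hour urine MA, and other indicators were used to evaluate TOD". None says which measure is used, for whom, or what follows if they disagree. Neither has a cut-off for damage, although 2.5.5 gives one for carotid IMT and a range for microalbumin (MA).

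Other parts of the plan that bear on this:

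- The heart measure in 2.5.5 is scaled to body size: "LVMI = LVM / body surface area". No such step is given for Ccr.
- Exposure (2.5.6) is not scaled: "Based on the quartiles of the 24-hour urine sodium, the enrolled population was divided into low sodium group", and so on up to a high sodium group.
- Group comparison (2.7): "One-way analysis of variance was used for comparison of means among multiple groups". Pearson correlation is also planned. Analysis of covariance is named for blood pressure variability only.
- Urine analytes (2.5.4): "The urine sodium, urine potassium, and urine protein were measured in the laboratory". Urine creatinine, which a measured Ccr needs, is not in that list.
- Eligibility (2.3.1.2) uses a third measure: "eGFR ≤45 mL/minute". No equation and no body-surface term is given.
- Height, weight and sex are collected (2.5.1).

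**The concern.** Serum creatinine and Ccr are not interchangeable. A higher creatinine reads as worse function and a higher Ccr as better. Both also depend on body size. Absolute clearance rises with body size at a given clearance per m², and serum creatinine rises if creatinine generation grows faster than clearance does. Sodium intake plausibly rises with body size too, so the sodium quartiles may differ in size, and a kidney measure not corrected for size can differ across them for that reason alone.

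Ccr has a second problem. It would come from the same 24-hour urine as the exposure, so an incomplete or over-long collection moves sodium and Ccr in the same direction.

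At stake is the salt-filtration result, one part of the stated aim. With salt and filtration truly unrelated, the plan could report better function with high salt, no relation, or worse function, depending on which measure is reported.

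**Working it through.** The plan gives no figure for this endpoint, so there is none to reproduce. The check asks what each measure shows when size-indexed GFR is unrelated to sodium.

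**From the documents:** n = 600, about 150 per quartile; quartiles of absolute 24-hour sodium; P < .05.

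**Assumed, not in the documents:** log-SD of BSA 0.11, of sodium 0.35; absolute GFR proportional to BSA; creatinine generation proportional to BSA to the power m, with m from 1 to 2; sodium-BSA correlation ρ from 0 to 0.4; urine-collection error with log-SD c.

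**Step 1: body size, no collection error.** The mean of a standard normal variable in its top quarter is 1.271, so top and bottom quartiles lie 2 × 1.271 = 2.542 SD apart. The log difference in BSA is D = ρ × 0.11 × 2.542. Ccr shifts by D and serum creatinine by (m − 1) × D. At ρ = 0.3, D = 0.0839, and exp(0.0839) − 1 = 8.75%.

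Simulated top-minus-bottom differences, with the share of 400 null trials of 600 patients in which the ANOVA rejects:

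| ρ | m | Serum creatinine | Ccr, unindexed | Ccr / BSA |
|---|---|---|---|---|
| 0 | 1.5 | 0.0% (0.04) | +0.1% (0.03) | +0.1% (0.04) |
| 0.2 | 1.5 | +3.1% (0.12) | +5.7% (0.39) | −0.1% (0.05) |
| 0.3 | 1 | −0.2% (0.04) | +8.9% (0.78) | +0.2% (0.07) |
| 0.3 | 1.5 | +4.3% (0.18) | +8.7% (0.76) | −0.1% (0.04) |
| 0.3 | 2 | +8.6% (0.57) | +8.5% (0.77) | −0.1% (0.03) |
| 0.4 | 2 | +11.9% (0.87) | +12.0% (0.96) | 0.0% (0.04) |

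Ccr moves whenever ρ is above 0. Creatinine moves only if m is also above 1.

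**Step 2: the same in clinical units.** A second null model assumes 55% men, mean BSA 1.82 m² (men) and 1.60 m² (women), indexed GFR 85 ± 14, age 60 ± 12, and creatinine generation from age, sex and weight. At ρ = 0.3, Ccr rises from about 81 to 88 mL/min from lowest to highest quartile (r = 0.16). Serum creatinine rises from about 70 to 77 µmol/L (r = 0.14), and indexed GFR stays at 85. At n = 600, P < .05 needs |r| of about 1.96 / √600 = 0.08. Because generation here follows weight, it rises faster than BSA, so this model lies towards the upper end of Step 1 for creatinine.

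**Step 3: shared urine collection, ρ = 0, Ccr indexed.** The covariance of log sodium and log Ccr is c². With c = 0.1, the SD of measured log sodium is √(0.35² + 0.1²) = 0.364. Taking the log-SD of indexed GFR as 14/85 = 0.165, the SD of log indexed Ccr is √(0.165² + 0.1²) = 0.193. So r = 0.01 / (0.364 × 0.193) = 0.14. The quartile difference is 2.542 × 0.01 / 0.364 = 0.070 on the log scale, or about +7%. In the Step 1 simulation (indexed-GFR log-SD 0.20) it was also about +7%, with rejection in 0.62 to 0.66 of runs. Indexing removes the size effect but not this one.

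**Step 4: would eGFR alone be enough?** In the Step 2 model at ρ = 0.3, eGFR from a common creatinine, age and sex equation falls from about 93 to 90 across quartiles (r = −0.08), because the equation has no body-size term. Adjusted for age, sex and BSA, the association is about 0.

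**The case against.** The strongest reply has four parts.

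**The size rests on outside assumptions.** This stands. With no link between sodium and body size, Step 1 gives nothing. A reader might infer that the two measures must give opposite answers. The documents do not support that: if creatinine generation is proportional to BSA, creatinine is flat and only Ccr moves. They then disagree, but not in opposite directions.

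**Adjustment may be planned.** Section 2.7 includes a stepwise regression whose candidate variables are not listed, and covariate lists are often left to an analysis plan. So body-size adjustment is not excluded. But it is not stated for kidney measures either, and the methods that are stated for comparisons other than blood pressure variability (one-way ANOVA, nonparametric tests and Pearson correlation) are unadjusted.

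**The selection rule may be elsewhere.** Figure 1 and Table 1 are not shown, and the kidney sentence in 2.5.5 is broken in the text as read. A reader might infer that the investigators intend to choose after seeing the data; nothing in the article shows that. What stands is that the alternative appears in three places, always without a rule.

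**Kidney damage is not only filtration.** A reader might infer that the whole salt-kidney question is open. It is not: 24-hour MA is a separate marker with its own range of 30 to 300 mg/24 hour, and the alternative does not touch it.

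**Conclusion.** The point holds for the filtration measure. The article leaves open which of two measures is the endpoint and states no body-size handling for either, while grouping patients by a quantity that plausibly depends on body size. For sodium-BSA correlations of 0.2 to 0.4 and no true salt effect, unindexed Ccr is 5.7% to 12.0% higher in the top sodium quartile than in the bottom one, and serum creatinine 0 to 11.9% higher. The Ccr figures rest on the assumed correlation and spread of BSA; the creatinine figures also rest on how creatinine generation scales with size. The shared-collection link (r about 0.14 at c = 0.1) needs no body-size assumption, but it does need a measured Ccr and imperfect collection.

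It would be too much to conclude that switching to eGFR alone removes the problem. It avoids the shared urine, but without size adjustment it still shows r of about −0.08 in the same null model.

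**What to change.** In the Objective, the Introduction and section 2.5.5, replace the alternative with one filtration endpoint for all patients: eGFR per 1.73 m² from serum creatinine, age and sex, with the equation named and lower values meaning worse function. Section 2.3.1.2 names no equation, so it cannot simply be cited for this.

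In section 2.7, state that this endpoint is compared across sodium quartiles by analysis of covariance, and related to sodium by regression, both adjusted for age, sex and BSA calculated from the collected height and weight. Report serum creatinine and BSA-indexed Ccr as descriptive only. If Ccr is to be measured, add urine creatinine to the analytes in 2.5.4.

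The cost is a few sentences and slightly more analysis. The eGFR endpoint needs no new measurement. The downside is small: a creatinine-based eGFR is less precise for an individual than a well-collected clearance.
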